### Cost-Effectiveness Analysis

Cost-effectiveness will be estimated using a health economic model developed for preliminary analysis of the APPROACH pilot feasibility trial [53]. The model is a cohort Markov model with annual cycles and a lifetime horizon, which links PA to mortality from cancer and other causes. The model will be updated using data from the study, reducing key uncertainties identified as part of the preliminary analysis. The model population will be updated using baseline characteristics from the study. PA changes due to the intervention incorporated in the model will be based on weekly METs rather than on the primary trial outcome, as this measurement aligns better with other data already included in the model defining the relationship between PA and mortality [17,103,104]. Additions to the model will be made to incorporate NHS resource use and quality-of-life data gathered as part of the trial, as these were not included in the previous modeling but are likely to have large impacts on cost-effectiveness. Intervention costs will also be updated. The model will estimate costs and quality-adjusted life years using probabilistic sensitivity analysis to enable uncertainty in the results to be captured. Cost-effectiveness will be estimated across the whole population and in relevant subgroups.

### Qualitative Analysis

Qualitative interview data will be analyzed using a framework analysis approach [105]. This approach was chosen because these interviews will inform the process evaluation of the intervention and data will fulfil predetermined information needs about the implementation of the intervention, mechanisms of action, and contextual factors impacting engagement [106]. We also anticipate mapping BCTs against the Behavior Change Taxonomy Ontology [62,63]. The Framework Method involves both deductive and inductive approaches to analyzing the data, where predefined codes are used alongside open coding [107]. There are 7 stages [107]: transcription, familiarization, coding, developing a working analytical framework, applying the analytical framework, charting the data into the framework matrix, and interpreting the data. This approach enables a systematic procedure for reducing the data while remaining flexible enough to identify unexpected themes and perspectives. Indexing of manuscripts will be undertaken by researchers not involved in the delivery of the intervention to minimize reflexivity biases. A portion of transcripts will be independently double-coded (with any ambiguities or differences discussed and resolved). Final reporting of the qualitative interview data collection and analysis process will be reported according to the COREQ (Consolidated Criteria for Reporting Qualitative Research) Checklist [108].

### Data Monitoring

UCL is the trial sponsor. The trial will be overseen by a Trial Management Group consisting of the chief investigators (AF and PL), co-investigators, and research staff employed on the grant. An external Trial Steering Committee, including 2 independent members, all co-investigators, and lay representatives, will be updated regularly on trial progress and will meet as required to provide input. No formal data monitoring committee will be set up, and there are no criteria for stopping the trial as walking is a very low-risk intervention.

### Adverse Event Reporting

All adverse events that the research team become aware of from the point of consent will be assessed by severity (mild, moderate, or severe), causality (not related, unlikely, possibly, probably, definitely, or not assessable), and expectedness (expected or unexpected). In this population, various expected adverse events relating to participant’s cancer diagnosis and treatment may occur (eg, acute illness, symptoms related to treatment), but as these would not be related to the intervention, they will not be recorded. All other adverse events will be recorded, including “mild skin irritation from the adhesive dressing when wearing the activPAL device” as this has been observed previously in older adults [109] and in the pilot [53].

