**Intervention: phone call or video call (2)**				
	Remind them of their target, and discuss if needs adapting			007011
	Ask how they are getting on with their target			007012
	Ask participants what is preventing them from walking and what would help them to start (if relevant)			007008
	Repeat any of the points from call 1 as appropriate			As relevant

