#### Behavioral Support Calls

Two semiscripted behavioral support video or telephone calls are undertaken by a trained researcher around one month apart. The first call takes place as soon after randomization as possible and introduces the recommendations around PA for people diagnosed with cancer (eg, 150 minutes of MVPA), how brisk walking is a form of moderate PA, the evidence for benefits of meeting these guidelines, and the importance of increasing PA by any amount (eg, highlighting the Every Movement Counts World Health Organization campaign) [72]. The researcher also explains how to form walking habits, how the app works, and encourages use of the app to help set and monitor goals (eg, “What do you want to aim for? One, two or three active tens [so 10, 20 or 30 minutes of brisk walking a day]”). Participants are encouraged to make plans and establish habits for using the app, plan to increase their brisk walking if appropriate, and use the app to track their progress. The call also aims to explore barriers to PA and explore ways of addressing them drawn from evidence (eg, treatment-related fatigue). This call is intended to replicate the type of conversation that a health care professional (eg, clinical nurse specialist) could have with patients as part of routine care. A second call is arranged for around 4 weeks later to see how participants are progressing, troubleshoot (eg, their plans or the app), and remind and recap on any information as required. With the participant’s agreement, calls are recorded to allow fidelity checks.

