### Control Group

Control group participants are notified of their group allocation by telephone or email, then receive “usual care” (no additional support beyond being informed in the information sheet that PA is beneficial for people after a diagnosis of cancer).

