#### Qualitative End of Study Interviews

A subsample of intervention participants (approximately n=20-30) will be interviewed after they have completed the 6-month data collection. These telephone or video call interviews will be semistructured (Multimedia Appendix 4 provides the interview guide), audio recorded, and will explore experiences of using the intervention materials, their walking experiences, and their use of the app.

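### Adverse-event capture is passive and only the intervention arm has scheduled support calls, so events may be ascertained unequally between arms

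*Protocol article*

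**What the plan says.** The protocol article, under Adverse Event Reporting, defines which events enter the data: "All adverse events that the research team become aware of from the point of consent will be assessed by severity", and also by causality and expectedness. Expected events arising from the cancer or its treatment are left out in both arms: "as these would not be related to the intervention, they will not be recorded". Table 1, which lists assessments as minor as an optional waist measurement, has no adverse-event item at any time point.

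Contact after randomization differs by arm:

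- **Intervention arm.** Under Behavioral Support Calls: "Two semiscripted behavioral support video or telephone calls are undertaken by a trained researcher around one month apart". Of the second call: "A second call is arranged for around 4 weeks later to see how participants are progressing, troubleshoot". Table 3 shows that the calls cover the effect of cancer and treatment on activity, worries about doing more, and obstacles to walking. Table 1 adds intervention-only feedback questionnaires at 3 and 6 months. Under Qualitative End of Study Interviews: "A subsample of intervention participants (approximately n=20-30) will be interviewed after they have completed the 6-month data collection".
- **Control arm.** Under Control Group: "Control group participants are notified of their group allocation by telephone or email". Usual care follows.

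Under Data Monitoring, the article says that no formal data monitoring committee will be formed and that "there are no criteria for stopping the trial as walking is a very low-risk intervention".

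**The concern.** When an event counts only if staff hear of it, the count depends on how often staff speak with participants and what they talk about. Here that differs by randomized arm. A researcher who asks how walking is going, and what gets in the way, is likely to hear of a fall, a sore knee or breathlessness. A control participant with the same event has no scheduled conversation in which to mention it.

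What is at stake is how the safety data are read. Counts by arm in a randomized trial will be set side by side whether or not a test is planned. If controls are under-detected, equal true risks could look like an excess with the intervention. With no data monitoring committee, the trial's own event records carry more of the safety assessment than they otherwise would.

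**Working it through.** **Is there a figure in the plan to reproduce?** Not on this point: the article states no adverse-event rate, no detection probability and no between-arm adverse-event comparison. The only design figure used below is the arm size. From Sample Size, 212 / 0.9 = 235.6, rounded up to 236 per arm, and 2 × 236 = 472, as stated.

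**Step 1. Set the routes of detection side by side.**

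| Route | Intervention | Control | Described as an adverse-event enquiry? |
|---|---|---|---|
| Two support calls (Behavioral Support Calls; Table 3) | yes | no | no |
| Feedback questionnaires at 3 and 6 months (Table 1) | yes | no | no |
| Interviews, about 20-30 people (Qualitative End of Study Interviews) | subsample | no | no |
| Reminder calls and help with questionnaires (Measures, Overview) | if needed | if needed | no |
| Self-reported service use at 3 and 6 months (Table 1; Health and Social Care Service Use) | yes | yes | no |
| Hospital records at 6 months, covering 30 weeks (same section) | yes | yes | no |
| Telephone support to build confidence (Limitations) | if needed | if needed | no |

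The first three routes exist in one arm only. The rest are shared. Service-use items and hospital records would mainly pick up events that led to care, and would probably miss a fall or muscle pain that did not.

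**Step 2. What unequal detection does to a ratio.** Let p be the true risk and d the probability that the team learns of an event.

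Observed ratio = (p_I × d_I) / (p_C × d_C)

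If the true risks are equal, p cancels and the observed ratio is d_I / d_C, whatever the true risk.

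**Step 3. Illustration.** Everything here except the 236 per arm is assumed: true risk 10% in both arms, and four pairs of detection probabilities. Expected count = 236 × 0.10 × d.

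| d_I v d_C | Intervention count | Control count | Ratio |
|---|---|---|---|
| 60% v 60% | 14.2 | 14.2 | 1.0 |
| 60% v 50% | 14.2 | 11.8 | 1.2 |
| 70% v 50% | 16.5 | 11.8 | 1.4 |
| 80% v 40% | 18.9 | 9.4 | 2.0 |

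The ratios restate the assumed inputs. They show how the bias would act and do not estimate it.

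**Step 4. Timing.** Results reports 473 participants randomized as of December 2025. The last assessment window closes 30 weeks after randomization (Measures, Overview). Anyone randomized more than 30 weeks before a change takes effect has passed both follow-ups, so a new question reaches only the remainder.

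**The case against.** The strongest reply has four parts.

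1. **No between-arm adverse-event analysis is planned.** Adverse events are absent from the aims and from Data Analysis. The article promises assessment and recording of individual events, and judging causality case by case does not need equal detection. This stands as to what is planned. It does not stop counts by arm from being compared by readers.
2. **The article condenses a full protocol that may hold an elicitation procedure.** That is possible, and an absent detail alone would be no finding. But the article states passive capture as the rule, and its own schedule is consistent with that rule. The point rests on what is stated.
3. **Both arms share several routes.** This is correct, and the gap is narrower than the calls alone suggest. The one event named for recording, skin irritation from the activity monitor, comes from a device worn on the same schedule in both arms. Some of what the calls bring out, such as treatment-related fatigue, may also fall under the exclusion of expected events.
4. **It is late to change.** This is also correct, and it limits what a new question can achieve.

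A reader might go further and infer that intervention counts are inflated, that adverse events are the trial's only safety evidence, or that the safety result cannot be read in either direction. The documents support none of these. No detection rate is given, so a risk of unequal ascertainment is as far as the text goes, and missed events in controls are a better description than excess events in the intervention arm. Service use, hospital contacts, fatigue, sleep, mood and quality of life are collected in both arms. And if detection is indeed better in the intervention arm, a result showing no excess there would be reassuring.

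**Conclusion.** The concern holds as a risk of unequal ascertainment, most likely through under-detection in controls. It rests on three features of the article: passive capture as the stated rule, no scheduled adverse-event enquiry, and live support calls and interviews in one arm only. Its size cannot be computed. Over the assumed detection pairs, equal true risks give observed ratios of 1.0 to 2.0, and the lower end, no distortion, is not excluded. The direction is an inference from the call content and is not stated in the documents. The primary endpoint and the sample size are unaffected. The point merits action because raw counts by arm would otherwise be open to misreading, and the remedy is cheap.

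**What to change.** 1. Add one short adverse-event question, worded identically for both arms, to the remaining 3- and 6-month questionnaires. Handle it through the follow-up team, which Measures already describes as blinded to allocation.
2. Record for every event how it was first learned of: questionnaire, hospital record, reminder or support contact open to both arms, support call, feedback questionnaire or interview.
3. Base any between-arm safety statement only on routes common to both arms, namely the questionnaire items and the 6-month hospital records, with the number of participants actually asked as the denominator for the new question.
4. Report events first learned of through intervention-only contacts separately, without a between-arm comparison.

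The cost is slightly longer questionnaires, a protocol amendment and more events to assess, with no new visits. Coverage will be incomplete: for participants who have already finished follow-up, only the source tagging and the shared-route restriction apply, and retrospective tagging depends on the event log having kept the source.

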#### Health and Social Care Service Use

Participants are asked to self-report their use of health and social care using items from the Client Service Receipt Inventory (CSRI), which has been validated against objective primary care records [100] and is recommended for usage of hospital and other community health services [101]. As part of the medical records data collection (undertaken by research staff at 6 months postrandomization), details about participant’s hospital-based treatment and care received (including the number of hospital contacts) during the 30-week trial period will be recorded.

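### Expected cancer- and treatment-related adverse events are presumed unrelated and left unrecorded, although the same section says all adverse events are graded for causality

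*Protocol article*

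**What the plan says.** The Adverse Event Reporting section has three relevant statements.

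- **General rule:** "All adverse events that the research team become aware of from the point of consent will be assessed by severity". The other two dimensions follow: "causality (not related, unlikely, possibly, probably, definitely, or not assessable), and expectedness (expected or unexpected".
- **Exception:** "various expected adverse events relating to participant’s cancer diagnosis and treatment may occur (eg, acute illness, symptoms related to treatment". The reason and the consequence come next: "but as these would not be related to the intervention, they will not be recorded".
- **Remainder:** "All other adverse events will be recorded, including “mild skin irritation from the adhesive dressing when wearing the activPAL device".

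Other sections bear on the point.

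- **Behavioral Support Calls** (intervention arm only): "Two semiscripted behavioral support video or telephone calls are undertaken by a trained researcher around one month apart".
- **Data Monitoring:** "No formal data monitoring committee will be set up, and there are no criteria for stopping the trial as walking is a very low-risk intervention". The same section sets up an external steering committee that includes two independent members.
- **Health and Social Care Service Use:** for all participants, "details about participant’s hospital-based treatment and care received (including the number of hospital contacts) during the 30-week trial period will be recorded".

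**The concern.** The causality scale exists to decide, for each event, whether the intervention played a part. The exception answers that question in advance for a whole class and gives the answer as the reason for keeping no record. If brisk walking worsened a treatment symptom in some participants, the event could be set aside as expected and treatment-related, leaving no grade to examine later. Expected and unrelated are different properties, and the general rule treats them as two separate scales.

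At stake is the completeness of the harms record for a population that can include people still having treatment or recently treated. A second issue concerns the events that are recorded: capture depends on the team becoming aware of them, and one arm has more researcher contact than the other.

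**Working it through.** The section gives no figure for this point, so the check compares the text with itself and with the rest of the article.

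**1. General rule against exception.** The general rule covers all adverse events the team learns of and offers six causality grades, only one of which is not related. Expectedness is graded separately in two levels. An expected event may therefore fall in any of the six grades. The exception treats the other 6 − 1 = 5 grades as empty for expected cancer- and treatment-related events. That is an assumption about the class, whereas the general rule calls for a judgement on each event.

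**2. Scope of the exception.** It covers expected events only. An unexpected event linked to cancer or treatment is still recorded under the remainder clause. So is an event that is not attributed to cancer or treatment, such as a fall on a walk. Within that limit the class is still wide, because acute illness is offered as an example without a boundary.

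**3. Exception against the trial's rationale.**
- The Introduction cites less fatigue and pain among the benefits of physical activity.
- Table 3 lists, as leaflet content, that activity improves treatment side effects.
- The Leaflet and Website section places those benefits during treatment as well as after it.
- Fatigue (FACIT-F) is a secondary outcome in Data Analysis.

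A trial that expects its intervention to improve treatment symptoms cannot also assume that a change in those symptoms is unrelated to it.

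**4. Who is enrolled.** Table 2 admits patients diagnosed within two years (up to 2.5 years at consent), requires six weeks since cancer surgery, and excludes performance status 3 or worse. Ongoing treatment is not an exclusion, so events in this class will arise in the trial.

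**5. Awareness by arm.** Table 3 shows that call 1 asks how cancer and treatment have affected activity, and that call 2 asks, where relevant, what is preventing walking. Behavioral Support Calls names treatment-related fatigue as an example of a barrier. Table 1 also gives feedback questionnaires and interviews to the intervention arm only. Controls have no counterpart to these contacts. Both arms have the 3- and 6-month assessments, with reminder calls and telephone help where needed.

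**6. Can the size be derived?** No. The share of events falling in the excluded class is not given. Quantifying unequal awareness would need the chance that a contact reveals an event and the number of comparable contacts per arm. The article states neither.

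**The case against.** The strongest reply has five parts.

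- **Assessing and recording are different steps.** The section can be read as grading every event and then logging all but the expected ones attributed to the cancer. That reading is possible, so the contradiction is not absolute. The stated reason fits it poorly, because it presumes a result instead of reporting one. An event that is not recorded also leaves no grade to audit.
- **No between-arm safety comparison is planned.** The aims are efficacy and cost-effectiveness, and Data Analysis lists no adverse event analysis. This stands. A reader might infer that the rule makes the trial's safety comparison uninterpretable. The article does not support that: it plans no such comparison, and all other adverse events are recorded.
- **Related data are collected alike in both arms.** Fatigue, sleep, anxiety, depression, quality of life and hospital contacts are all measured, so worsening fatigue would be visible in FACIT-F. This stands and limits the harm. Scale scores and contact counts are still not events with a causality grade.
- **Oversight exists.** The steering committee has independent members, and a data monitoring committee could not review unrecorded events either. The absence of such a committee is therefore not the defect.
- **The full protocol (version 9.0) may define expected events.** That could narrow the class. It would not remove the rule as the article states it.

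A reader might also be tempted to put a risk ratio on unequal awareness. Call 1 takes place as soon as possible after randomization, before much exposure, and reminder or support calls can occur in both arms. Any such ratio would rest on assumed detection probabilities and contact counts.

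**Conclusion.** The concern holds in limited form. The section states a rule that replaces individual causality grading with a presumption for expected cancer- and treatment-related events, and that presumption conflicts with the trial's own premise. An adverse event summary by arm would omit a class selected by presumed cause, so it could not show a difference between arms in that class. Among the events that are recorded, awareness could be higher in the intervention arm.

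The conclusion rests on the article's wording and assumes that version 9.0 applies the same rule. The size of either effect is unknown. The efficacy and cost-effectiveness aims do not rest on the adverse event log. This should be corrected, but it does not threaten the primary analysis.

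**What to change.** 1. Remove the sentence that presumes non-relatedness, so that causality is graded for each event.
2. Log every adverse event the team learns of in either arm, including expected cancer- and treatment-related ones, with its causality and expectedness grades.
3. Note how each event came to light. In summaries by arm, list separately those learned only on intervention calls. This matters more once the exclusion is lifted, because the call script invites mention of treatment problems.
4. Report as a limitation that earlier events in the excluded class were not recorded.

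The cost is a wording change, more event lines to enter and grade, and one extra field for source. No new visits or instruments are needed, because the change covers only events the team already hears about. It cannot recover what has been lost: the Results section reports 473 participants randomized by December 2025. The last participant is due to finish in 2026, so the change can still apply to follow-up that remains.
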